# Systems analysis and improvement approach to optimize tuberculosis (SAIA-TB) screening, treatment, and prevention in South Africa: a stepped-wedge cluster randomized trial

**DOI:** 10.1186/s43058-024-00582-z

**Published:** 2024-04-16

**Keywords:** Capacity building, Implementation science, Infectious disease, Sub-Saharan Africa

## Abstract

**Background:**

The use of systems engineering tools, including the development and use of care cascades using routinely collected data, process mapping, and continuous quality improvement, is used for frontline healthcare workers to devise systems level change. South Africa experiences high rates of tuberculosis (TB) infection and disease as well as HIV co-infection. The Department of Health has made significant gains in HIV services over the last two decades, reaching their set “90–90-90” targets for HIV. However, TB services, although robust, have lagged in comparison for both disease and infection. The Systems Analysis and Improvement Approach (SAIA) is a five-step implementation science method, drawn from systems engineering, to identify, define, and implement workflow modifications using cascade analysis, process mapping, and repeated quality improvement cycles within healthcare facilities.

**Methods:**

This stepped-wedge cluster randomized trial will evaluate the effectiveness of SAIA on TB (SAIA-TB) cascade optimization for patients with TB and high-risk contacts across 16 clinics in four local municipalities in the Sarah Baartman district, Eastern Cape, South Africa. We hypothesize that SAIA-TB implementation will lead to a 20% increase in each of: TB screening, TB preventive treatment initiation, and TB disease treatment initiation during the 18-month intervention period. Focus group discussions and key informant interviews with clinic staff will also be conducted to determine drivers of implementation variability across clinics.

**Discussion:**

This study has the potential to improve TB screening, treatment initiation, and completion for both active disease and preventive measures among individuals with and without HIV in a high burden setting. SAIA-TB provides frontline health care workers with a systems-level view of their care delivery system with the aim of sustainable systems-level improvements.

**Trial registration:**

Clinicaltrials.gov, NCT06314386. Registered 18 March 2024, https://clinicaltrials.gov/study/NCT06314386. NCT06314386.

**Supplementary Information:**

The online version contains supplementary material available at 10.1186/s43058-024-00582-z.

Contributions to the literature
Our study examines if delivery of a user-friendly, low-cost package of systems engineering tools co-delivered iteratively by study personnel and district managers in a low-resourced, public sector health system improves health system performance and patient outcomes.Research on systems engineering tools has largely come from high-resourced health systems, with little data from low- and middle-income countriesThis is the first trial of the systems analysis and improvement approach (SAIA) for TB in a low-resource, high-burden setting.

## Background

Tuberculosis (TB) has been a leading infectious disease killer globally for decades despite the availability of robust diagnostics, effective prevention, and treatment [1]. One challenge has been poor implementation of comprehensive TB programs in low-resource settings where the majority of the global TB burden lies [2–12]. Additionally, one billion people are estimated to be infected with TB globally, with 5–15% of people at risk of becoming sick with TB disease [1]. Therefore, tackling TB systematically clinic by clinic and at the community level is important. Molecular testing and whole-genome sequencing have shown that in high-burden settings, the majority of household contacts have unmatched sensitivity patterns to the index patient in their household, thus inferring they were not infected in the household, but rather in a community setting [13–16]. So, although household contacts are a known high-risk group to screen for TB, using innovative methods to engage and empower clinics and communities in screening measures among high-risk populations is key to close existing case-detection gaps [17–19]. People living with HIV (PLH) are an important high-risk population to focus efforts on, as HIV is a leading driver for TB and TB is the leading cause of death among PLH [1, 20].

HIV is a main driver of TB in South Africa, one of 30 high burden TB countries, with nearly 60% of people newly diagnosed with TB also co-infected with HIV [20, 21].The TB care cascade evaluates gaps in care along the sequential steps of care for individuals with TB [22]; in South Africa, losses have been measured at multiple steps: 5% at test access, 13% at diagnosis, 12% at treatment initiation, and 17% at successful treatment completion [23]. These individual “gaps” in the cascade mount up to a 57% loss across the full TB care cascade in South Africa. The inequity in gaps is more stark among individuals coinfected with HIV and especially among individuals with drug-resistant TB with an overall 88% loss for those with drug-resistant TB [23]. Increasing the proportion of individuals eligible to complete each step of the care cascade is essential to reduce the TB burden, as those individuals who go undiagnosed and untreated contribute to further TB transmission and many of those diagnosed failing to complete the cascade [1, 24].

Even less is known about the care cascade for TB prevention treatment (TPT) [25, 26]. An estimated 80% of South Africans are infected with TB [21, 27]. This has created a vast reservoir of people at risk of progressing to TB disease, especially recent contacts of TB patients and PLH [28, 29]. Therefore, it is imperative to screen and treat not only TB disease but also subclinical TB infection in this high burden setting [30]. This is critical as South Africa recently updated their TPT guidelines, expanding eligibility to all household contacts in late 2021 [31]. Understanding how guidelines can be optimized is critical to implementation success and sustainability [32]. A global meta-analysis of the TPT cascade from 2016 revealed that of individuals intended for TB screening, less than 19% successfully completed TPT, indicating an opportunity to leverage strategies to close gaps in TB care [25].

There is growing international recognition for interventions to end the TB epidemic; gaining political will, community acceptance, avoiding stigma, and emphasizing feasibility of eliminating TB are all critical [33, 34]. Passive case finding (PCF)—the notion of waiting until individuals become symptomatic with TB disease to report to the health system—is the most common form of case finding. However, this is insufficient to reduce TB incidence and prevalence. Rather, a systematic and comprehensive active case finding (ACF) strategy must be employed where programs search for and screen high-risk groups to detect disease at an earlier stage, ideally before further transmission [35]. Recently the WHO Asia–Pacific region published ACF optimization implementation lessons and evidence for achieving TB elimination, including 17 studies assessing community- and household-based TB programs focused on detection, prevention, and treatment [36]. These, along with other historical examples of TB elimination in Alaska, Greenland, and Australia, provide necessary examples of scalable implementation efforts [37–40].

The Systems Analysis and Improvement Approach (SAIA) is an evidence-based implementation strategy designed to optimize cascade performance, is feasible for frontline healthcare workers and managers, and may be applicable to optimize TB care [41]. We aim to adapt SAIA for TB (SAIA-TB), expanding upon successful SAIA adaptations that have been trialed across a range of clinical settings, in sub-Saharan Africa and the USA, and leverage preliminary TB cascade data collected in this setting [4, 5, 41–47]. Preliminary work developing the SAIA-TB cascade by the investigative team has identified six routinely collected TB data points to serve as linked steps across TB services (screening, evaluation, diagnosis, linkage to care, treatment completion, and TB-free survival). The resultant TB cascade analysis tool (TCAT) will be refined as part of the SAIA-TB implementation strategy to aid frontline healthcare workers and managers to optimize cascade performance. In addition to the TCAT which is specifically tailored to the TB care cascade in our proposed study setting, SAIA-TB will also employ monthly process flow mapping and continuous quality improvement cycles with clinic-led discussions to implement clinic-identified micro-interventions to optimize the TB care delivery for patients as each of these components are core to the SAIA strategy [48].

### Goals and objectives

In this study, we will (1) evaluate the effectiveness of SAIA-TB use in clinics on TB cascade outcomes for TB patients and with high-risk contacts (specifically among PLH) and (2) determine the drivers of SAIA-TB implementation success or failure across clinics.

## Methods

### Description of the SAIA-TB implementation strategy

SAIA-TB is similar to previously described SAIA applications [44, 48, 49]. The facility-based, five-step iterative process is designed to guide clinic staff and managers in understanding and improving their TB services and optimizing MOH-defined evidence-based interventions, namely, TB screening, prevention, and treatment protocols in order to improve patient outcomes through clinic teams’ delivery of these protocols. The SAIA-TB implementation strategy uses tools borrowed from systems engineering to strengthen the care teams view of TB delivery at their facility—across the care cascade from TB screening to TB-free survival. Using routinely collected data and health systems knowledge, the tools guide clinic staff’s identification and prioritization of modifiable barriers, followed by continuous quality improvement cycles to implement and rapidly evaluate appropriate clinic-level solutions (Fig. 1). SAIA-TB includes the following steps.

**Fig. 1 Fig1:**
[figure not shown]
Adapted systems analysis and improvement approach cycle for TB (SAIA-TB)

#### Step 1

Understand targeted TB cascade performance and identify priority areas for improvement. The TB cascade analysis tool (TCAT) (Fig. 2) uses routine data to provide a rapid, systems-level view of drop-offs along the TB cascade for outpatient clients and priority sub-populations (PLH, children under 5 years, and household contacts), with an optimization function allowing the user (i.e., clinic staff) to rapidly assess how many additional people will be served if only one step is fully optimized while other steps stay the same [42]. As an analytic tool, TCATs help frontline staff and clinic managers to prioritize where to intervene by providing a view of the greatest potential for flow improvements across the entire cascade. This tool calculates the number and proportion of individuals flowing through each step of the TB cascade, broken down into the flow from screening through treatment completion.

**Fig. 2 Fig2:**
[figure not shown]
TB cascade analysis tool (TCAT)

#### Step 2

Process mapping to identify clinic-level modifiable bottlenecks in TB management. Enabling facility-level staff to identify and gain consensus on bottlenecks to address in their TB systems essential to defining innovations to implement. SAIA-TB applies sequential patient process flow mapping procedures, along with workflow observation, to identify bottlenecks and guide discussion on opportunities for modifications across the care team [50, 51]. Study personnel will work with clinic staff, across all services and staff levels, to map the existing pathways patients with TB and high-risk individuals (PLH, children under 5 years, and household contacts) take at their facility.

#### Step 3

Define and implement clinic-specific workflow adaptations to address modifiable bottlenecks. After identifying modifiable barriers within cascade steps, clinic staff identify a simple, specific change to improve performance within the targeted step. Selected workflow adaptations should be feasible to implement, be within the scope of influence of clinic management and frontline staff, and be expected to lead to rapid, substantial improvements in the targeted cascade step. Ideas for adaptations will arise from brainstorming solutions with clinic staff, complemented by best practices from the literature and high performing services in South Africa (i.e., HIV services) and other TB programs [22, 49]. An implementation plan for the innovation is described in writing by clinic and study personnel to ensure consensus among clinic staff, and to clarify operational design and roles, including a future state process map that reflects processes after the modification. After defining the adaptation to be implemented, clinic staff will implement the proposed changes.

#### Step 4

Monitor changes in routine performance and initiate additional iterations. Clinic staff monitor change in routinely reported data from the TB cascade step selected for improvement. Measuring the absolute change in the proportion of patients progressing through targeted steps captures large, rapid improvements accompanying modifications.

#### Step 5

Repeat cycle. Systems engineering improvement processes are by definition iterative, with ongoing testing of innovations responsive to evolving, contextually specific barriers. Clinic staff will repeat steps 1 through 5 at the end of each cycle to identify novel approaches to modify previously identified barriers or, if the first cycle was successful, focus on improving priority bottlenecks identified [44, 49]. Steps 3 through 5 are analogous to continuous quality improvement [44, 49].

### SAIA-TB trial design

This study is a 5-year, four-wave stepped wedge cluster randomized trial design to assess the effectiveness of the SAIA-TB strategy (Fig. 1; Consort Checklist, Additional file 1). Each wave includes four local municipalities within a district, with four health facilities per local municipality purposively selected to receive SAIA for a total of 16 facilities. Each local municipality represents a cluster and will be randomized for intervention wave. Each facility will have at least 12 months of baseline data collection followed by 18 months of intervention and 12 months of a measured maintenance phase (Fig. 3).

**Fig. 3 Fig3:**
[figure not shown]
SAIA-TB study design and study timeline

### Process for introducing SAIA-TB

#### Pre-implementation and baseline data collection

SAIA-TB’s standard operating procedures (SOPs), including the delivery and training schedules and intervention guides and tools (TCAT, process mapping, and continuous quality improvement guides), will be refined from in preparation for the SAIA-TB trial. In the 12 months prior to SAIA-TB implementation, the study team will engage in *baseline data collection* to ensure routine data points needed to populate the TCAT are collected reliably and are available at all facilities (Fig. 4). The project manager (a professional nurse) will conduct a baseline facility-level assessment (described below) and introduce the study to facility teams with a brief orientation on SAIA-TB background and SAIA main components (including an overview of the TCAT, process mapping, and continuous quality improvement guides), as well as share the implementation schedule, and begin data collection procedures. Baseline data collection will continue for at least 12 months in all clinics with monthly reporting of TCAT variables with support from study personnel.

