### Outcomes

We will measure each indicator across the TB care cascade from TB screening to TB-free survival. (Table 2). Primary outcomes include the mean change in proportion of individuals (1) screened for TB disease, (2) initiated on TPT, or (3) initiated on TB disease treatment combined across all facilities during the intervention period (exposed) compared to baseline (unexposed). Primary outcomes were selected based on sensitivity to system-level improvements; they represent SAIA-TB steps that, if changed, would meaningfully alter patterns of TB-related morbidity and they are routinely collected. They are relatively easy to collect and readily understood by clinic managers and frontline staff. Indicators will be assessed monthly over the study period (including 12 months baseline, 18 months intervention, and 12 months maintenance phase).

**Table 2 Tab2:** SAIA-TB primary and secondary outcomes

SAIA-TB primary and secondary outcome variables	
**TB indicator (variable)**	**Numerator/denominator**
TB screening^a^	*#screened with WHO symptom screen* # target population
TB evaluation	*# receiving a diagnostic evaluation (GXP/LAM)* # positive screening
TB diagnosis	*# diagnosed with TB (GXP/LAM/clinical)* # who completed a diagnostic evaluation
Linkage to care for TPT^a^	*# initiating TPT* # negative diagnostic evaluation + eligible for TPT
Linkage to care for TB disease^a^	*# initiating TB treatment* # positive diagnostic evaluation
Successful TPT outcome	*# completing TPT* # initiating TPT
Successful TB outcome^b^	*# cure or complete treatment for TB disease* # initiating TB treatment
TB-free survival	*# TB-free (CXR/GXP) 12 months* *after initiating TPT or TB disease treatment* # successful outcomes for TPT or TB disease

*CXR* Chest x-ray, *GXP* GeneXpert, *LAM,* Urine lipoarabinomannan

^a^Primary outcome variable

^b^WHO definition

Secondary outcomes include the additional TB cascade indicators (TB evaluation, diagnosis, treatment outcome, and TB-free survival); however, some of these are more dependent on a mix of individual-level factors (i.e., adherence to medication) (Table 2). These indicators are clinically important and can be affected at a system-level. Outcomes will be assessed for all patients receiving care, as well as assessed by important sub-groups, such as by HIV status, age (under 5 years), and local municipality (cluster).

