### Data sources

Patient-level TB data will be sourced from existing programmatic Ministry of Health facility registries and patient-level forms. Slight modifications may need to be designed to capture the entire TB care cascade from screening to TB-free survival. Data will be abstracted from these existing paper registries and patient forms at least weekly by study personnel into a study database via REDCap on tablet or laptop [53]. As part of routine care, each patient with TB is assigned a unique identification number that links across service points and clinics, which will be used to abstract registry data for study outcome measures. The database will generate on-demand reports with monthly indicators to populate the TCAT.

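### Baseline months serve both to make the screening records reliable and as the unexposed comparator, so better recording can be counted as more TB screening

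*Protocol article*

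**What the plan says.** - **Outcome and source.** In Table 2 the numerator of the screening indicator is the number "screened with WHO symptom screen", divided by the target population. Under Data sources, "Patient-level TB data will be sourced from existing programmatic Ministry of Health facility registries and patient-level forms". Study personnel abstract these paper records at least weekly.
- **Comparator.** Under Outcomes, the primary contrast is "combined across all facilities during the intervention period (exposed) compared to baseline (unexposed"). The Exposure definition treats a facility as unexposed until the intervention starts in its municipality, so every baseline month counts as comparator time.
- **Task of the baseline months.** Under Pre-implementation and baseline data collection, the study team works in the 12 months before implementation "to ensure routine data points needed to populate the TCAT are collected reliably and are available at all facilities". All clinics report "with monthly reporting of TCAT variables with support from study personnel".
- **Change of forms.** Under Data sources: "Slight modifications may need to be designed to capture the entire TB care cascade from screening to TB-free survival". No date is given.
- **What starts at crossover.** Under Intervention phase, staff practise filling in and reading the TB cascade analysis tool (TCAT), with supervision visits every two weeks for a month and monthly after that. Under Step 4, "Clinic staff monitor change in routinely reported data from the TB cascade step selected for improvement".
- **Model.** Data analysis names a generalized linear mixed model with clustering by municipality. It lists months since study start among the adjustments whose impact will be examined. A segmented time series is a secondary analysis.

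**The concern.** Recorded screening is true screening multiplied by the completeness of recording. The effect estimate is valid only if completeness does not differ between unexposed and exposed time, beyond what the model removes. The article gives two reasons why it might differ.

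1. **A gain within baseline.** If early baseline months are under-recorded and recording improves as the study team works on it, the comparator is lowered and later months look better.
2. **A gain at crossover.** Once coaching starts, clinic teams follow the recorded figure for the step they have chosen to improve. More complete recording would then begin in the same month as exposure.

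Screening is the outcome on which the trial is sized. An error of this kind lies in the measurement, so a larger sample makes a biased estimate more precise but no less biased.

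**Working it through.** **Inputs from the article.** Baseline screening 39%; detectable difference 5%, read here as percentage points; 978 per cluster-period; intracluster correlation 0.01; alpha 0.05 (taken as two-sided); 4 clusters; 5 periods; waves 3 months apart; at least 12 baseline and 18 intervention months.

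**Assumed.** All completeness values. The documents give none.

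**1. The plan's own figure.** 978 × 5 = 4,890 and 4,890 × 4 = 19,560, as stated. The standard error comes from the Hussey-Hughes variance

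Var = Iσ²(σ² + Tτ²) / [(IU − W)σ² + (U² + ITU − TW − IV)τ²]

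with I = 4, T = 5, U = 10, W = 30, V = 30. The mean binomial variance is (0.39×0.61 + 0.44×0.56)/2 = 0.24215. Then σ² = 0.24215×0.99/978 = 0.000245 and τ² = 0.24215×0.01 = 0.00242. The bracket is 10σ² + 30τ² = 0.0751, and the standard error is about 0.0127, or 1.27 points. Power for 39% to 44% is about 97.6% (97.5% to 97.8% across variance conventions), close to the stated 99%. The point does not depend on that small gap.

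**2. Completeness needed to mimic the design difference.** True screening = 0.39 / c0, where c0 is completeness at baseline. Completeness that gives a recorded 44% is c1 = 0.44 / (0.39 / c0).

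- c0 = 75%: true 0.520; c1 = 0.44/0.520 = 84.6%.
- c0 = 80%: true 0.4875; c1 = 0.44/0.4875 = 90.3%.
- c0 = 85%: true 0.459; c1 = 95.9%.
- c0 = 90%: true 0.433; c1 would have to be 101.5%, so the full 5 points cannot arise from recording alone.

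**3. What time adjustment removes.** Noise-free monthly data were built with starts at months 12, 15, 18 and 21 and 18 intervention months each. True screening was held at 52% (0.39/0.75). The table shows the false effect in percentage points.

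| Recording pattern (assumed) | Crude | Cluster only | Cluster + linear month | Cluster + categorical month |
|---|---|---|---|---|
| Common ramp 75% to 90% over 12 months | +3.1 | +3.1 | −0.6 | 0.0 |
| Common ramp 75% to 90% over 6 months | +1.7 | +1.7 | −1.3 | 0.0 |
| 10-point jump at each crossover | +5.2 | +5.2 | +5.2 | +5.2 |
| Common ramp 75% to 85% over 12 months, plus 10-point jump | +7.3 | +7.3 | +4.8 | +5.2 |

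The jump is 0.52 × 0.10 = 5.2 points, and 5.2/1.27 is about 4 standard errors. Categorical month removes the common ramp completely. A linear month term overcorrects it. No form of calendar time removes the jump.

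**The case against.** The best reply is that the design already deals with much of this. Baseline collection runs in all clinics, so a recording gain from it is largely a shared calendar-time change, and a stepped wedge with month effects removes such a change. Making data reliable before crossover should also shrink any jump at crossover. Monthly reporting is already study-supported in baseline, staff receive an overview of the TCAT then, and study personnel abstract the data throughout. Routinely collected outcomes are a deliberate choice in a pragmatic trial, and checks on register quality may sit in procedures or an analysis plan that are not shown.

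Most of this stands. The first part, however, depends on month being in the primary model, and the article does not commit to that. Early strengthening makes a jump smaller but does not exclude one, because coached use of the TCAT starts only at crossover. The possible absence of quality checks is not part of this point.

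A reader might infer four stronger things that the documents do not support:

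- **That recording gains will be counted as screening whatever the analysis.** A gain common to all clinics gives no bias with categorical month.
- **That the registers are known to be incomplete.** Aiming for reliable collection is not evidence of a deficit, and the 39% comes from preliminary and national data, not from an audit of these 16 clinics.
- **That a symptom screen leaves no trace except one register entry, made by the coached staff.** The article names patient-level forms as well as registers. That clinic staff make the entries is a fair inference, not a statement.
- **That forms will change at crossover, or that the screening field will change.** The article says only that modifications may be needed to cover the whole cascade.

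**Conclusion.** The point holds as a risk of measurement bias in the primary screening outcome, not as a demonstrated error. The months that form the comparator are also months in which recording is being improved, and the article fixes neither the date of any form change nor calendar time as a term of the primary model.

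Its size is conditional. With true screening unchanged, a rise in completeness of about 10 points from a start of 75% to 80% reproduces the whole 5-point design difference. From a start of 90% it cannot. If the gain is common to all clinics, the bias is about 2 to 3 points in an unadjusted contrast under the ramps assumed here, and zero with categorical month. If the gain falls at crossover, it passes in full into every model considered. The secondary segmented time series would not settle the matter, because it uses the same records and would show the same step. The change is worth making before crossover, since a comparator of uncertain quality cannot be repaired afterwards.

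**What to change.** 1. **Freeze the records first.** Finalise registers and forms in all 16 clinics, and define the first comparator month as one that begins after that date. Treat earlier months as a run-in outside the primary comparison. Allow no form change at crossover.
2. **Fix time in the primary model.** State that categorical calendar month is a term of the primary model, not an adjustment to be explored.
3. **Add a supporting measure.** Report the number receiving a GXP/LAM evaluation divided by the same target population as the screening outcome, fitted with the same model. Table 2 divides evaluations by positive screens, so that indicator cannot show whether more of the target population was evaluated. If recorded screening rises and this measure does not, report the rise as not corroborated. Do not label it a recording change automatically: added true screens may be mostly negative and lead to few evaluations. The measure also comes from the same records and can move for its own reasons, so it supports the reading but does not decide it.

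**Cost.** Some early baseline months are lost. Study status dates the baseline assessments to October 2023 and the planned start to January 2025, so up to about 15 months may exist for the first wave and, with 3-month steps, more for later ones. Steps 2 and 3 need a little more analysis and only counts that Table 2 already requires. Step 1 removes form changes as a cause of a jump. It does not remove a jump caused by coaching, which remains a limitation to state when results are reported.
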